## Abstract

**Background:**

Sarcopenia is a clinical syndrome characterized by the loss of muscle mass and strength. Hormonal changes that occur early in women may influence protein synthesis and promote muscle atrophy, leading to probable sarcopenia, defined as a loss of muscle strength without an obvious decrease in muscle mass. Various types of exercise have already proven effective in treating sarcopenia. Power training (PT), a subtype of resistance training performed at high speed, has not yet been studied in this population group.

**Methods:**

A randomized controlled trial will be conducted with three parallel groups: a PT group, a multicomponent training (MT) group, and a no-exercise group. The inclusion criteria will be women over 65 years of age who meet the diagnostic criteria for probable sarcopenia (Hand grip test less than 16 kg and Five Times Sit to Stand Test more than 15 s) according to the European Working Group on Sarcopenia in Older People (EWGSOP2). Two assessments will be conducted at the beginning and at the end of the 32 weeks of intervention, in which variables of body composition (muscle, fat and weight) and functionality (strength and physical performance) will be collected. There will be 3 sessions of 50 minutes per week in each intervention group. The masking strategy will be double-blind. The analysis of intergroup differences will be conducted using multivariate and univariate analysis of variance (MANOVA and ANOVA), as well as pairwise comparisons (Bonferroni corrections). Changes in the degree of sarcopenia and how many women eliminate the risk of sarcopenia (no probable sarcopenia) after the different interventions will be tested.

**Discussion:**

The study aims to investigate the impact of PT in older women at risk of sarcopenia. The expected results are that PT will significantly improve functionality and body composition compared to other forms of exercise (MT) and no physical activity. The results may represent a significant advance in understanding and addressing sarcopenia before it becomes established, providing preventive treatment and new tools whose clinical applicability has been studied.

**Trial registration:**

The clinical trial was prospectively registered at ClinicalTrials.gov Identifier: NCT05870046.

## Background

The process of ageing is a biological phenomenon that results in increased susceptibility to disease and a decline in functional capacity [1]. This phenomenon has resulted in a notable increase in the proportion of the population that is ageing, driven by rising life expectancy and declining birth rates [2]. The concept of healthy ageing is defined by five dimensions: metabolic and physiological health, physical function, cognitive function, psychological well-being and social well-being. Among these dimensions, physical function is closely associated with sarcopenia [3].

Sarcopenia is a clinical syndrome characterised by the loss of muscle mass and strength [4]. Aging causes an estimated 1–2% annual loss of muscle mass starting at age 50 years, with a total loss of 45% by age 80 years [5]. The onset of hormonal changes that result in muscle atrophy occurs earlier and progresses more gradually in women than in men. The loss of muscle mass and function, leading to postmenopausal sarcopenia, may be attributed to the gradual decline in oestrogen and androgen levels [6]. This reduction may result in alterations to the secretion of growth hormone and insulin-like growth factor 1, as well as an increase in pro-inflammatory cytokines that promote sarcopenia [7–9]. Furthermore, the decline in progesterone, which plays a pivotal role in regulating the menstrual cycle, also contributes to the development of sarcopenia in older women [10]. These hormonal changes render women more susceptible to sarcopenia at an earlier age than men, whose hormonal decline typically occurs around the age of 80 [11].

Sarcopenia is associated with an increased risk of falls, fractures, physical disability, and mortality [12]. The International Classification of Diseases (ICD-10: M62) formally recognises it as a muscle disease [13]. Sarcopenia is a geriatric syndrome frequently found in older adults, with a worldwide prevalence ranging from 10% to 27% [14]. In recent years, various international groups have published diagnostic criteria for sarcopenia, all using the same tools and tests, but with different cut-off points [15–19]. In Europe, the guidelines recommended by the European Working Group on Sarcopenia in Older People 2 (EWGSOP2) are generally followed. Probable sarcopenia is defined as loss of muscle strength without obvious loss of muscle mass (>5.5 kg/m2 in women and >7 kg/m2). In women, probable sarcopenia is established if the hand grip test (HG) value is less than 16 kg and it takes more than 15 seconds to perform the five times sit-to-stand (5STS) test [15].

Scientific evidence has shown that exercise is currently the main intervention available to combat sarcopenia [20]. A systematic review has shown that different modes of physical training can improve sarcopenia in older adults [21]. The most researched types of exercise are MT and resistance training (RT). Although it has been shown that RT may be more effective than MT in the prevention of muscle loss and functionality, MT also shows good benefits being one of the most practiced types of exercise by older adults [21–23]. RT stimulates satellite cell proliferation and protein synthesis, which are important for maintaining muscle homeostasis in adults with sarcopenia [24]. However, there are different subtypes of RT, such as power training (PT), which involves high contraction speeds.

In healthy older adults PT has been shown to have a greater impact on improving muscle power and physical performance compared to RT. Additionally, it has been shown to reduce the incidence of falls, demonstrating superior effects on functionality than RT in older adults, including strength variables that diagnose probable sarcopenia [25, 26]. However, the effect of PT on older women in the preclinical stage of the disease (probable sarcopenia according to EWGSOP2) has not yet been investigated.

### Aim

In line with the above, the main objective is to assess and analyse the effect of a muscle PT program on muscle condition and degree of sarcopenia, evaluating muscle strength, body composition and functionality in women over 65 years of age with sarcopenia probable, comparing it with a MT intervention and women who do not perform physical exercise.

## Material and methods

### Design and setting of the study

A 1-year, prospective, longitudinal, parallel-group, randomized controlled trial will be conducted. Two experimental groups PT group, MT group and a non-exercise control group will be formed. The reporting of this clinical trial conforms to the Consolidated Standards for Reporting Trials (CONSORT 2010) statement [27]. The development of this clinical trial protocol follows the standards of the SPIRIT statement (Standard Protocol Items: Recommendations for Interventional Trials) (S1 Table) [28]. The schedule of enrolment, interventions and assessments as detailed in Fig 1 following recommendations of the SPIRIT 2013 Statement (Fig 1)

**Fig 1 pone.0313072.g001:**
[figure not shown]
The schedule of enrolment, interventions, and assessments of SPIRIT 2013.

The protocol for this trial received approval from the Salamanca Health Area Drug Research Ethics Committee with code PI 2023061317 and was conducted in accordance with the Declaration of Helsinki [29]. The clinical trial was registered in ClinicalTrials.gov (NCT05870046).

All participants will be members of the Geriatric Revitalization Program (GRP) and will exercise at their respective senior centres. Selection criteria will be applied to determine eligibility. Eligible participants from the same senior centre will be grouped together and randomly assigned. As the sessions are held in different centres in Salamanca, only 5 to 15 participants will be allowed to take part in each centre.

The randomization will be performed using R software version 4.2.1 by an external statistician who will not participate in the analysis.

Blinding will be based on the study hypothesis and the participants assigned to each group. The strategy employed will be double-blinding. Both the assessors and the statistical researcher will be blinded. The external researcher responsible for randomization will inform each instructor which intervention to administer in each group. The evaluators will not know the assignment of the groups and that the confidentiality of the identification of the participants and their codes will be maintained. The researchers who will teach the exercise sessions will not participate in the evaluations of the study outcome variables. The participants will know the type of intervention due to its nature, but they will not know what type of exercise or the study hypothesis. Blinding will not be disclosed under any circumstances. The study methods flow chart can be seen in Fig 2.

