#### Interventions

All study participants will continue with their medical treatment guidelines, level of physical activity, and dietary pattern. Two parallel intervention programs will be designed; the control group will not receive any intervention. The exercise sessions, which will be conducted by healthcare professionals with more than one year’s experience in providing exercise sessions for older adults, will be held at senior centres throughout the city. Adherence to the program will be verified by daily attendance at exercise sessions.

The PT and MT sessions will follow the ACSM recommendations and the basic principles of the FITT-VP (frequency, intensity, type of exercise, time, volume and progression) are followed [44]. There will be three 50-minute sessions per week for 32 weeks. The sessions will begin and end with common exercises, starting with active mobility and ending with stretching and diaphragmatic breathing. The load progression will be based on individual perceived exertion. At the end of each week, participants will be asked to rate their perceived exertion using the modified Borg scale. If the score is less than 7, the intensity of the exercises will be increased for the following week to maintain a consistent level of 7 on the scale. The experienced health personnel delivering the sessions will determine how to progress, such as increasing external weight, repetitions, sets, reducing rest time, or performing unilateral exercises. Although these are group sessions, progression and volume will be adjusted on an individual basis, due to the variability of comorbidities that older adults may present.

The rooms in the senior centres for the interventions will maintain a uniformity in their infrastructure, ensuring in all cases an environment conducive to the optimal realization of the intervention sessions. To encourage adherence, attendance will be collected for each session. If they do not attend, they will be called to their attention, even warning that they may be excluded. Although the number and duration of sessions will be identical in both groups, the nature of the intervention will be different for each study group, and participants will remain unaware of their assignment to a specific group.

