### Data analysis

Statistical analysis will be performed using an intention-to-treat (ITT) approach. Baseline differences between groups will be tested using normality plots and the Kolmogorov-Smirnov test. Homogeneity between groups will be assessed using Levene’s test, thus ensuring successful randomisation. Missing data will be handled using the imputation method of the last observation carried forward. It will be decided to keep outliers in the analysis, as they may represent legitimate outliers or relevant information, which will be discussed in the future study.

A descriptive analysis of the dependent and independent variables of each group will be carried out. Quantitative variables will be expressed as mean ± standard deviation, while qualitative variables will be presented as frequency distributions and percentages.

To assess the effect of the interventions on the study variables in each group, multivariate analysis of variance (MANOVA) will be used as the main method. The variables will be grouped into two large blocks: those measuring functionality (HG, 5STS, GS, TUG, Two-minute step test and SPPB) and those measuring body composition (weight, WC, BF%, visceral fat, ASM, SMI and BMI). Subsequently, MANOVA will be performed on the difference in means after the intervention, using time as an intra-group factor and type of intervention as an inter-group factor. To graphically represent the MANOVA, the canonical Biplot will be displayed, including the confidence circles representing the set of variables in each intervention group. If the circles do not overlap, it can be concluded that there are significant differences between the groups.

To verify the results of the MANOVA, differences between groups for each quantitative variable, both functional and body composition, will be analysed using the repeated measures univariate analysis of variance (ANOVA) test for normal and homogeneous variables or the Kruskal-Wallis test for non-normal or heterogeneous variables. As an additional method, pairwise comparisons will be performed using Bonferroni’s test for normal and homogeneous variables and Dunn’s test for non-normal and heterogeneous variables to determine between which groups there are significant differences.

The effect size in ANOVA of the results obtained in each group will be measured by eta squared (η^2^). Values around 0.01 indicate a small effect size, around 0.06 a medium effect size, and 0.14 or more a large effect size.

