### Rigour

This study has been developed in accordance with the recommendations supported by the SPIRIT Declaration 2013 regarding the essential content of a clinical trial protocol (see S1 Table). Furthermore, the study design follows the guidelines established by the CONSORT 2010 guidelines for the execution of parallel group randomized controlled clinical trials.

For effective description and replication of the proposed intervention, the TIDieR checklist is included as an additional tool (see S3 Table).

Upon completion of the study, the data collected here will be made available to those investigators who request it through FAIR sharing of research data repositories at https://www.re3data.org/.

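### Women are grouped by senior centre and trained in groups, but the sample size and every planned test treat them as independent, and the unit of randomisation is unclear

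*Protocol article*

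**What the plan says.** **Allocation (Design and setting of the study).** Participants "will exercise at their respective senior centres". The article continues: "Eligible participants from the same senior centre will be grouped together and randomly assigned". It adds that "only 5 to 15 participants will be allowed to take part in each centre", and that "The external researcher responsible for randomization will inform each instructor which intervention to administer in each group".

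**Delivery (Interventions).** Both exercise programmes run for 32 weeks as shared sessions: "Although these are group sessions, progression and volume will be adjusted on an individual basis".

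**Design label.** "A 1-year, prospective, longitudinal, parallel-group, randomized controlled trial will be conducted". The Rigour section cites CONSORT 2010 for "parallel group randomized controlled clinical trials". No cluster design is named.

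**Sample size.** The inputs are three groups, two-sided alpha 0.05, beta 0.2, a difference of 2.5 units, SD 5 and 20% loss, giving 105 women at 1:1:1. No cluster size, ICC or design effect is listed.

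**Analysis (Data analysis).** The MANOVA is specified "using time as an intra-group factor and type of intervention as an inter-group factor". The repeated-measures ANOVA or Kruskal-Wallis tests, and the Bonferroni or Dunn comparisons, likewise have no centre or training-group term.

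**The concern.** Women who train together for eight months share an instructor, a room and a group. If whole centres are allocated, everyone in a centre also gets the same arm. A centre with a good instructor or high morale then moves several women in one arm together, and a test that counts each woman as a separate unit takes that shared movement for evidence about the treatment.

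At stake is the trial's main claim, that PT outperforms MT and no exercise. With only a few centres per arm, one unusually successful centre could yield a significant difference. Bonferroni does not help: it adjusts for the number of comparisons, not for a standard error that is too small.

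**Working it through.** **1. Number of centres.** At 15 per centre, 105/15 = 7 centres. At 5 per centre, 105/5 = 21. That is about 2 to 7 centres per arm.

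**2. The plan's own sample size.** n per arm = 2(1.96 + 0.84)² × 5²/2.5² = 63. With 20% loss, 63/0.8 gives 79 per arm, or 237 in total. The stated 105 is not reproduced. This is a separate defect, but it sets the starting point for power: 105 women are 35 per arm, and 35 × 0.8 = 28 evaluable per arm.

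**3. Design effect.** DE = 1 + (m − 1) × ICC, where m is the number of women per centre. The article gives no ICC, so 0.01 to 0.10 is assumed.

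| Women per centre | ICC 0.01 | ICC 0.05 | ICC 0.10 |
|---|---|---|---|
| 5 | 1.04 | 1.20 | 1.40 |
| 10 | 1.09 | 1.45 | 1.90 |
| 15 | 1.14 | 1.70 | 2.40 |

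**4. Type I error, whole centres allocated.** With two time points, the group-by-time test in a repeated-measures ANOVA equals a one-way ANOVA on change. That ANOVA was simulated with no true difference, a random centre effect and about 35 women per arm, and tested at a nominal 5%. Separate runs of 8,000 and 20,000 replicates agreed to within about one percentage point.

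| Centres per arm × women | ICC 0.01 | ICC 0.05 | ICC 0.10 |
|---|---|---|---|
| 7 × 5 | 6% | 8% | 12% |
| 5 × 7 | 6% | 10% | 16% |
| 4 × 9 | 6% | 12% | 19% |
| 3 × 12 | 7% | 14% | 25% |

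**5. Type I error if women are randomised individually.** Here only PT and MT are clustered, by training group, and controls are independent. At ICC 0.05 the same ANOVA rejects in about 7% (7 groups of 5), 8% (5 of 7), 10% (4 of 9) and 11 to 12% (3 of 12).

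**6. Pairwise power for 2.5 units at SD 5.** With 28 evaluable per arm and no clustering, power is about 45%. With 10 centres, the between-centre degrees of freedom are 10 − 3 = 7. Taking m = 10, the effective n per arm is 28/1.09 = 25.7, 28/1.45 = 19.3 and 28/1.90 = 14.7. The noncentrality is (2.5/5) × √(n/2) = 1.79, 1.55 and 1.36. Against a t distribution on 7 df, power is about 34%, 27% and 22% at ICC 0.01, 0.05 and 0.10.

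**The case against.** **The unit of allocation is not certain.** The allocation sentence is terse. The Evaluations section describes subjects, not centres, being allocated, and the sample size counts subjects at 1:1:1. A reader might infer that this is definitely a cluster-randomised trial, but the article does not settle it. The centre cap and the instruction to each instructor favour the centre reading. Under the other reading the inflation is smaller but does not vanish (step 5).

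**The label is not itself wrong.** A reader might infer that the article calls the trial individually randomised. It says only parallel-group, which a cluster trial can also be.

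**Stable centre differences cancel.** The planned analysis compares change over time, so fixed differences between neighbourhoods drop out. This stands: the relevant ICC is that of change in outcome. It is unknown, and at 0.01 the inflation is slight.

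**A later analysis plan may add a centre term.** That would answer an omission. Here the article itself states the sample-size inputs, the model factors and the tests, and as stated they treat women as independent.

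**Conclusion.** The point holds. The article sets up grouping by centre and delivery in groups, then fixes a sample size and analyses that ignore both. Where change in outcome is correlated within centres or training groups, p values will be too small and intervals too narrow.

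The size rests on the assumed ICC and on the number of centres. Over ICC 0.01 to 0.10, the true error of a nominal 5% ANOVA runs from about 6 to 12% with seven centres per arm and from about 7 to 25% with three. The 25% figure is the upper end of these settings, not the expected value. The simulations cover a single-outcome ANOVA; the MANOVA and rank tests were not simulated.

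Two stronger readings are not supported. The power of 22 to 34% is not all due to clustering, because power is already about 45% without it. Nor can it be said that an arm will end up with a single centre: the article does not describe the type of randomisation list.

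**What to change.** 1. State the actual unit of randomisation and the number of centres per arm. If the unit is the centre, allocate equal numbers of centres to each arm where allocation is not yet done, and report under the CONSORT cluster extension.
2. Analyse each primary variable (five times sit-to-stand, hand grip) with a mixed model: final value on baseline value and arm, with a random centre effect. If women are randomised individually, use a random training-group effect in PT and MT instead. Use Satterthwaite or Kenward-Roger degrees of freedom.
3. Report the estimated ICC, and restate power or the detectable difference over a stated ICC range with the design effect included. Correct the starting figure of 105 first.

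**Cost.** Wording, an allocation list if still open, and a mixed model in place of ANOVA. Intervals will be wider and stated power lower. These changes need no added participants and no new measurements, only that centre or training group is recorded for each woman. They do not restore 80% power; at 10 per centre the design effect alone would take 105 to between 115 (105 × 1.09) and 200 (105 × 1.90).

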### Limitations

The study protocol has limitations that should be communicated to inform the interpretation of the results and the design of future research. Although the study follows all CONSORT recommendations, participating subjects will not be blinded to the intervention due to the nature of the intervention. Given the variability of the factors that may affect this population group, not all of them will be assessed, including dietary patterns and different diseases such as diabetes. The expected results cannot be extrapolated to the general population, to other population groups (such as hospitalized or institutionalized older adults) or to different environments or city. This sample was chosen because older women, the population group that lives in the community, probably represent the most people who may be at risk of sarcopenia. We have prioritized obtaining results with a homogeneous sample over generalizing them to the general population.

Progression during the intervention will be based on each participant’s perception of effort, which may introduce biases as some participants may overestimate or underestimate their effort. Although the physical therapist will instruct participants on how to determine their perceived exertion, it is important to note that their unfamiliarity with this method may affect the results.

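### The trial is labelled double-blind and participants are said to be unaware of their group, but by the protocol's own account only assessors and the statistician are masked

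*Protocol article*

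**What the plan says.** The protocol article describes masking in four places.

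- Abstract, Methods: "The masking strategy will be double-blind". Nothing there says who is masked.
- Design and setting of the study: "The strategy employed will be double-blinding", followed directly by "Both the assessors and the statistical researcher will be blinded". The section then says of the women: "The participants will know the type of intervention due to its nature, but they will not know what type of exercise or the study hypothesis". It also states that the external researcher who randomises tells each instructor which programme to deliver.
- Interventions: for the control arm, "the control group will not receive any intervention". Later, in a sentence that opens by noting equal session numbers and durations in both groups, it says that "participants will remain unaware of their assignment to a specific group".
- Limitations: "participating subjects will not be blinded to the intervention due to the nature of the intervention".

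Three further facts bear on assessor masking. The design section says that eligible women from one senior centre are grouped together and randomised, with 5 to 15 women per centre. It also says that evaluators do not know the allocation and that instructors do not assess outcomes. The Evaluations section places baseline before randomisation, holds the assessments at the Faculty, and has one investigator perform all tests in a standardised way set out in a supplementary table that is not shown.

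**The concern.** The word double-blind usually tells a reader that participants are masked. Here they cannot be, at least between exercising and not exercising, and the Limitations section says as much. The label and the Interventions sentence therefore credit the trial with a protection that it lacks.

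This matters because of the primary outcomes. Hand grip and five times sit-to-stand are performance tests, and the result depends partly on how hard the woman tries. A woman who has trained for 32 weeks, or who joined an exercise programme and was allocated to none, may try more or less at the final test because she knows this. Someone who reads only the abstract would take a difference between power training and control as protected against that effect.

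**Working it through.** No figure in the plan has to be reproduced, because the point rests on setting statements side by side.

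**Who is masked, by the protocol's own account**

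| Role | Statement in favour of masking | Statement against |
|---|---|---|
| Participants | Abstract label (unqualified); Interventions: "participants will remain unaware of their assignment to a specific group" | Design section: "The participants will know the type of intervention due to its nature"; Limitations: not blinded |
| Instructors | None | Design section: told which programme to deliver |
| Assessors | Design section: masked, not told the allocation | None |
| Statistician | Design section: masked | None |

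**Step 1. Participants.** Taken at face value, the Interventions sentence and the Limitations sentence cannot both be true. The design section's own sentence is hard to follow: women know the type of intervention but not the type of exercise.

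**Step 2. Which comparisons are affected.** Three arms give 3 × 2 / 2 = 3 pairwise comparisons. Two of them (power training against control, multicomponent training against control) set three sessions a week for 32 weeks against none, so a woman must know which side she is on. For the third, power against multicomponent training, some masking is conceivable: an exerciser may not know which programme is expected to do better.

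**Step 3. Which measurements are exposed.** Baseline precedes randomisation, so knowledge of the arm cannot affect it. Only the final assessment is exposed, and with two assessments in all, that measurement determines the change from baseline.

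**Step 4. Assessor masking, for scale only.** Inputs: 105 women (Sample size section) and 5 to 15 per centre (design section).

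- Number of centres: 105 / 15 = 7 to 105 / 5 = 21.
- Centres per arm at 1:1:1: 35 / 15 = 2.3 to 35 / 5 = 7.
- Share of the sample in one centre: 5 / 105 = 4.8% to 15 / 105 = 14.3%.

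If whole centres are allocated, and if the assessor can link women to centres, one remark about a centre's programme could reveal the arm of those women from that centre who are still to be tested. That is at most 5 to 15 women. Both conditions are assumptions. Allocation by centre is the natural reading of the design section, but it is not fully explicit, and the article does not say whether the assessor knows each woman's centre.

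**The case against.** The strongest reply is that the design section defines its term. Straight after the label it names assessors and statistician, so double can be taken to mean those two roles, and the Limitations section openly concedes that participants are not blinded. This stands in part: someone who reads the whole article is not misled about who is masked. It does not rescue the unqualified abstract, nor the Interventions sentence.

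A second reply concerns that sentence. Its opening refers to sessions in both groups, which can only mean the two exercise arms. Read with the design section, it may mean that exercisers are not told which programme is under test. That reading is coherent and is a reason to reword the sentence instead of deleting it. The sentence does not say so, however, and as written it covers participants in general. A claim of hypothesis masking would also have to fit the Ethical aspects section, which says that women are informed of the project's objectives before consent.

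A reader might go further and infer that assessor masking fails because centres are allocated together. The documents do not support that. Evaluators are not told the allocation, codes are confidential, instructors do not assess, baseline comes before randomisation, and testing takes place away from the senior centres under a standardised procedure. Unmasking through a remark at the final visit is a possible route, not a stated failure, and the full protocol may already address it.

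A reader might also want a figure for effort bias as a share of the 2.5-unit target difference. The article gives neither baseline means nor any information on how far effort shifts these tests, so any such figure would only restate its assumptions.

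**Conclusion.** The masking claim is wrong as written for participants. The label in the abstract and the design section, and the sentence in Interventions, do not agree with the design section's list of masked roles or with the Limitations section. The error is clearest for the two comparisons with the no-exercise control, where concealment from the woman is impossible and both primary outcomes depend on effort. For power against multicomponent training, the most that the text could support is that women are not told which programme is expected to be superior.

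The size of any bias cannot be derived from the documents. The consequence is for interpretation: a difference from control cannot be presented as free of participant expectation. Allocation, outcomes, sample size and analysis are unaffected. Masking of assessors and statistician is stated and stands, with a residual risk at the final visit that rests on the two assumptions in step 4. The correction should be made, but it is one of description and safeguard and not a fault that undermines the trial.

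**What to change.** 1. In the abstract and the design section, replace the double-blind label with: *assessor- and analyst-blind; participants and instructors not blinded*.
2. Reword the Interventions sentence to agree with the design section and Limitations. At most it should say that women in the two exercise arms are not told which programme is hypothesised to be superior, and only if the consent information is consistent with that. Clarify the matching sentence in the design section in the same way.
3. State that both comparisons with the no-exercise control are open-label for participants and will be interpreted with that in mind.
4. Ask women not to mention their centre or programme at the final assessment.

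Uniform encouragement during the hand grip and sit-to-stand tests may already be in the supplementary table of test procedures; a cross-reference would then be enough. Recording the assessor's guess of the arm is optional.

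The cost is a few changed sentences and one instruction at the final visit, with no extra staff or participants. The stated masking becomes less favourable, but it matches the design.
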